## Abstract

**Background:**

Older people often suffer from multimorbidity resulting in polypharmacy. The correct administration of medication is a crucial factor influencing treatment efficacy. However, tools for evaluating the ability to self-administer different dosage forms of medications are lacking. The objectives of the ABLYMED study are to 1) assess the ability to self-administer different dosage forms of medication in older non-demented in-hospital patients who report autonomous management of medication, 2) identify factors influencing the ability to self-administer medication, and 3) develop a standardized tool to validly assess the ability to self-administer different dosage forms of medications based on the final study results.

**Methods:**

One hundred in-patients from the department of orthopedics and trauma surgery of the University Hospital Düsseldorf  ≥ 70 years of age and regularly taking ≥ 5 different drugs autonomously will be prospectively recruited into the observational cross-sectional single-center ABLYMED study. Patients undergo an interview addressing demographic and clinical information, medication history (which medications are taken since when, in which dose and dosage form, and subjective proficiency of taking these medications), medication adherence, and factors possibly influencing adherence including personality traits and perceived quality of the medication regimen. Quality of the medication regimen is also rated by clinicians according to validated lists. Further, patients receive a comprehensive geriatric assessment including measures of cognition, mobility, and functional status. The ability to self-administer medication is assessed by having patients perform different tasks related to medication self-administration, which are video recorded and rated by different experts. The patients’ self-reported ability will be correlated with the observed performance in the self-administration tasks. Further, factors correlating with the reported and observed ability to self-administer medication will be evaluated using correlation and regression models. Based on the final study results, a novel tool to assess the ability of older patients to self-administer medication will be developed.

**Discussion:**

In addition to guideline-based pharmacotherapy, correct intake of prescribed medication is crucial for optimal therapy of multimorbidity in older people. Tools to validly assess the ability of older patients to self-administer different dosage forms of medications are lacking, but should be included in comprehensive geriatric assessments to secure functional health.

**Trial registration:**

Development of an assessment instrument to evaluate the ability to manage various dosage forms**,** DRKS-ID: DRKS00025788, (date of registration: 07/09/2021).

## Background

More than half of the older population ≥ 65 years of age suffers from chronic diseases and multimorbidity [1]. As a result, polypharmacy also increases with age [2] and is associated with negative clinical outcomes such as adverse drug events, drug interactions, potentially inappropriate prescriptions, functional decline, cognitive impairment, falls, hospitalization, and reduced adherence to medication [3]. Of note, underuse of adequately prescribed drugs is associated with negative clinical outcomes as well [4]. Higher complexity of a medication regimen including different dosage forms (e.g., pills, drops, pens, patches, or inhalers), high frequency of intake, or special intake requirements is associated with lower medication adherence leading to underuse of prescribed drugs [3]. Older individuals with polypharmacy are especially at risk of reduced adherence to a complex medication regimen because of their higher rate of impairment in physical and mental function including reduced vision, hearing, manual dexterity, mobility, and cognitive abilities [5].

Up to now, only the influence of handling errors of inhaler devices on the treatment efficacy of obstructive pulmonary disease has been investigated in more detail in older subjects [6–8]. These studies showed a high prevalence of problems with handling different inhalers [6–8] and a moderate association between the number of attempts required to ensure the correct use of the inhalers and the patients’ manual dexterity and cognitive skills [6]. The ability of geriatric patients to take pills out of different kinds of packaging has been investigated before showing that about 10% could not open blister packages, while more than 50% could not open child-resistant packaging. Failure to open pill packaging was associated with poor vision, cognitive function, and manual dexterity [9]. Additionally, the process of handling different dosage forms of medication has not been evaluated in an objective manner, even though this knowledge is crucial for the success of pharmacotherapy and the planning of support by nursing staff.

Therefore, the aims the ABLYMED study are to 1) assess the ability to self-administer different dosage forms of medication in older non-demented in-hospital patients who report autonomous management of medication, 2) identify factors influencing the ability to self-administer medication, and 3) develop a standardized tool to validly assess the ability to self-administer different dosage forms of medications based on the final study results.

Practical consequences of the ABLYMED study include prescription of nursing support in case of insufficient patient abilities to self-administer medication and adaptation of the medication regimen to the preserved abilities to handle medication in case patients can still partially handle their medication. This will improve patients’ quality of life and help to allocate limited healthcare resources in a reasonable way.

## Methods/design

### Study design and setting

This cross-sectional single-center observational study takes place at the department of orthopedics and trauma surgery at the University Hospital Düsseldorf, Germany. With more than 50,000 in-patients per year and more than 1,200 beds, the University Hospital Düsseldorf is the largest hospital of the state capital of North Rhine-Westphalia, Germany. About 9500 employees work in 29 clinical departments and 30 institutes. The percentage of patients ≥ 70 years of age treated in the department of orthopedics and trauma surgery is about 25%. These elderly patients are being taken care of in a specialized geriatric subdivision.

### Study population

Eligible for inclusion in the study are patients ≥ 70 years of age regularly taking ≥ 5 different drugs autonomously who are admitted to the department of orthopedics and trauma surgery electively or via the emergency department. We intend to include 100 patients as a pilot sample to obtain a sufficiently large dataset for performing correlational and regression analyses. Since there is no previous evidence, it was not possible to perform sample size calculation for our specific research question. The only previous study analyzing a related research question, which observed that the ability of geriatric patients to open pill packaging was significantly associated with vision, cognitive function, and manual dexterity [9], recruited a similar sample size as planned in or study (n = 119). Patients are recruited continuously until the planned sample size is reached. Study participation is voluntary and does not affect further treatment.

#### Inclusion criteria

In-patient at the department of orthopedics and trauma surgery at the University Hospital Düsseldorf, GermanyAge ≥ 70 yearsRegularly taking ≥ 5 different drugs autonomouslyWritten informed consent

#### Exclusion criteria

Dementia diagnosis (ICD-10-code F00-F03)Legal careInsufficient ability to self-administer medication at home (nursing service or help from family/friends)Insufficient ability to communicate (language barrier for foreign or migrant patients, severe presbyakusis)Poor vision (not able to read information written on medication packaging)Agraphia (inability to write)Alexia (inability to read)Instable clinical condition (intensive care requirement)Permanently bedriddenPalliative condition (life expectancy < 6 months)

### Objectives

#### Main objectives

Identification of problems to handle medication in different dosage formsIdentification of factors which are associated with the ability to self-administer medicationIdentification of the need for support in handling medicationDevelopment of a standardized tool to assess the ability to self-administer medication

#### Secondary objectives

Analysis of the interdependency betweenadherencecomplexity and quality of medication regimenobserved ability to self-administer medicationreported ability to self-administer medicationcognitive abilities and personality traitsdemographic / clinical characteristics

### Study procedures

#### Inclusion of patients

After arrival at the ward of the department of orthopedics and trauma surgery of the University Hospital Düsseldorf, all eligible patients receive an information brochure and are asked to participate in the study by the principal investigator (HF). The patients are given sufficient time to discuss participation with their family, friends, or general practitioner. Further, they can clarify remaining questions with the principal investigator. After informed consent is given and signed by the patient, he/she enters the study. The study was approved by the ethics committee at the faculty of medicine of the Heinrich Heine University Düsseldorf. Patients should use their daily support such as glasses and hearing aids during the study assessments.

#### Measures

##### Patient characteristics

In a face-to-face interview, the following patient characteristics are assessed:Sex (male, female, diverse)Age (years)Body weight (kg)Height (cm)Handedness (right, left, ambidextrous)Housing situation (single-person household, multi-person household, nursing home)Marital status (open response format, later classified as single = never married, married = living together with a partner, living apart = married but separated, widowed)Education level (open response format, later classified according to International Standard Classification of Education [10])Last profession (open response format, later classified according to International Standard Classification of Occupations [11])Reason for the current hospitalization (open response format, later classified according to the German modification of the International Classification of Procedures in Medicine [OPS])

##### Medication history

In a face-to-face patient interview with supporting medication lists, the following information regarding current medication are assessed:Drug name, active ingredient, Anatomical Therapeutic Chemical (ATC) code, strengthDosage formDoseDuration of prescriptionSelf-rated proficiency of taking the respective medication (German primary school grading system from 1 (very practiced/experienced) to 6 (not at all practiced/no experience)

Based on the information of the above-mentioned assessment of medication history, the *quality of pharmacotherapy* is assessed according to the FORTA principle [12], the PRISCUS list [13], and the Beers list [14]. In addition, *complexity of the medication regimen* is assessed according to the German version of the Medication Complexity Score (MRCI-D) [15] and *anticholinergic burden* is assessed according to the anticholinergic burden score for German prescribers (ACB-Score-G) [16]. The medication review is performed by a pharmacist (AM) and a geriatrician (HF).

##### Medication adherence

Medication adherence is assessed via a face-to-face interview using the German version of the Medication Adherence Report Scale (MARS-D) [17]. This questionnaire asks for the frequency of non-adherent behavior using 5 items scored on a 5-point Likert scale (1 = always, 2 = often, 3 = sometimes, 4 = rarely, 5 = never). The total score ranges from 5 to 25, with higher scores indicating better adherence to the prescribed medication.

In addition to the MARS-D, the patients answer questions about factors possibly influencing their adherence behavior. These questions were created by the authors based on own ideas and observations, literature review, and expert surveys. Questions refer to general health, beliefs about taking the right amount of medication, taking helpful medications, not having too many changes in medication, tolerance/side effects of medication, actual/needed support regarding medication intake, failures regarding medication management as well as problems regarding vision, swallowing, recognizing medication, and application of different dosage forms.

##### Medication management skills

In a face-to-face interview, medication management skills are assessed with a modified version of the medication management instrument for deficiencies in the elderly (MedMaIDE) [18]. The MedMaIDE was developed in the USA to assess deficiencies in medication management in community-dwelling older adults with non-medical staff. The MedMaIDE is based on subjective questionnaire data and direct observations of medication-taking behavior. It consists of 20 items covering 3 domains considered important for medication management: 1) what a person knows about the medication he/she is taking (knowledge; 8 items); 2) whether a person knows how to take his/her medication (administration; 6 items); and 3) whether a person knows how to get his/her medication from a doctor or pharmacy (procurement; 6 items). Critical items have been identified within each domain (5 for knowledge and administration each, and 3 for procurement), and are used in calculating the deficiency subscores for each domain and a total deficiency score. If a person is not able to answer an item/perform a task correctly for all prescribed medications, he/she gets a score of 1; thus, higher scores indicate higher deficiency in managing medication. For the ABLYMED study, the MedMaIDE was translated into German by a forward–backward translation procedure performed by a professional translation agency, and only the critical items are used.

##### Video-based evaluation of self-administration of medication

A new method was developed to assess the ability of patients to self-administer medication in different dosage forms in their original packaging (A tablets, B eye-drops, C oral drops, D insulin pen, E patch, F inhaler). The application of each dosage form is explained via an instructional video. Patients perform the tests to assess their ability to self-administer medication in different dosage forms twice (except inhaler test) in a modified order (group 1: ABCDEFEDCBA, group 2: FEDCBAABCDE) to control for sequence effects. Patients’ performance is video recorded, for each dosage form and each trial a separate video film is taken. The different dosage forms should be applied as follows:

A TabletsOn the table in front of the patient there are two packs of tablets (one including white tablets in an aluminum blister pack and one including blue tablets in a tablet tube), a pill organizer, and a pill cutter. The patient is asked to put one white tablet each for morning, noon, and evening and one blue tablet for the night into the pill organizer and close the organizer. The patient is then asked to open the pill organizer again, take out the blue tablet, divide it into two halves with the pill cutter, and put one half for the night back into the pill organizer.B Eye-dropsOn the table in front of the patient there is a one-dose ophtiole dispenser. The patient is asked to open the ophtiole dispenser.C Oral dropsOn the table in front of the patient there is a child-resistant dropper bottle and a teaspoon. The patient is asked to open the dropper bottle and drop 10 drops onto the teaspoon.D Insulin penOn the table in front of the patient there is an insulin pen. The patient is asked to dial in 12 units and inject it into a ball.E PatchOn the table in front of the patient there is a packed patch. The patient is asked to unpack the patch, peel off the protective liner without touching the sticky part too much, and apply it to the skin of the arm.F InhalerIf the patient's medication already includes a metered-dose inhaler/dry-powder inhaler, the inhalation technique is evaluated according to the validated scoring system developed by Zambelli-Simões et al. [19]. Thereafter, the inspiratory flow rate is measured for each patient at different resistances using the In-Check Dial G16 (MPV Medical GmbH, Munich, Germany). For this purpose, the patient is asked to breathe in slowly and deeply through the mouthpiece at each resistance setting.

If the patients have difficulties during the self-administration of medication, the experimenter can provide verbal or practical assistance, which is documented.

In 30 patients the assessment is repeated after 5 days to assess test–retest reliability.

Based on the video recordings, 2 independent raters evaluate the patient’s ability to self-administer different dosage forms of medication with a standardized assessment form. In a pilot phase, the form is presented to 15 different raters to evaluate the video recordings of 3 different patients. If the raters encounter problems leading to low interrater agreement, the form will be adapted. For each dosage form and each trial separately, the quality of the video is rated as good, moderate or unusable, with moderate indicating that for example the video starts too late or does not have an optimal focus, and unusable indicating that videos are missing or performance cannot be evaluated at all. Thereafter, each step of the medication administration is scored on a 5-point Likert scale (5 = not possible, meaning practical assistance needed or interruption; 4 = severe difficulties, meaning execution hardly possible or success of therapy at risk; 3 = moderate difficulties, meaning execution significantly slowed down; 2 = mild difficulties, meaning execution slightly slowed down; 1 = no difficulties, meaning correct and fluid execution).

The following steps of medication administration were defined:For tablets: taking the white tablets out of the packaging, taking the blue tablet out of the packaging, cutting the blue tablet, putting all tablets correctly into the pill organizerFor eye-drops: opening the ophtiole dispenserFor oral drops: opening the dropper bottle, targeting at the teaspoon, correct number of drops on the teaspoonFor insulin pen: removing the cap from the pen, removing the cap from the needle, dialing in the right dose, injectionFor patch: opening the packing, peeling off protective liner, sticking onto the armFor inhaler: see Zambelli-Simões et al. [19]

Finally, a global impression of the ability to self-administer the respective dosage form is scored on a 5-point Likert scale (5 = very bad, 4 = bad, 3 = moderate, 2 = good, 1 = very good).

##### Motor function/functional state

A hand dynamometer (Jamar™ hand dynamometer) is used to measure grip strength of the right and left hand. The maximum handgrip strength correlates well with total muscle mass. A hydraulic pinch gauge (Saehan Model SH 5005) is used to measure tip pinch strength of both hands. In tip pinch, the tip of the index finger and thumb hold the objects and the measure indicates direct strength of the 2 fingers.

To estimate everyday function of the hand and fingers, the patient is asked to open a bottle of water closed by a screw cap, which is rated as successful or not successful.

The grooved pegboard test (Lafayette Instrument®, Model 32,025, https://lafayetteevaluation.com/products/grooved-pegboard) is used to assess manual dexterity and complex visual-motor coordination. The patient is asked to put small pegs into 25 holes on a board as fast as possible. The grooved pegs must be inserted exactly and as soon as possible into appropriately shaped holes of the board. The test is executed with both hands separately, beginning with the dominant hand. For the right hand trial, pegs are placed from the patient’s left to right, for the left-hand trial from right to left. The time the patient needs to perform each trial is recorded. A trial is interrupted after 300 s. In addition, the number of drops and the number of correctly placed pegs per trial is noted. The test is explained to the patient with the help of an instructional video.

As an indicator for appendicular skeletal muscle mass, we determine the circumference of the mid upper arm and the calve at the area of its largest extent [20].

Triceps skinfold thickness is an indicator of subcutaneous fat, which is a proxy for total body fat. Triceps skinfold thickness is measured with a skinfold caliper (Fat Control Inc). With the subject's arm in a relaxed position, the skinfold is picked with thumb and index fingers at the middle of the back of upper arm.

History of falls is assessed in a face-to-face interview and categorized as 1 fall within the previous 12 months, 1 fall within the previous 3 months, or more than 1 fall within the previous 3 months.

The de Morton Mobility Index (DEMMI) [21] was developed to measure mobility in hospitalised older acute medical patients across a broad spectrum of mobility from bed bound to independent mobility. It consists of 15 mobility tasks which vary from easy (such as turning around while lying in bed) to demanding (such as placing the heel of one foot directly in front of the other with eyes closed for 10 s). The raw score is transformed to range from 0 to 100%, with lower scores indicating lower mobility.

The interview-based Katz index [22] assesses dependence in activities of daily living including bathing, dressing, going to the toilet, transferring, continence, and eating. It comprises 6 items, the total score ranges from 0 to 6, with lower scores indicating higher dependence.

The interview-based Barthel index [23] assesses dependence in activities of daily living similar to the Katz index, but in more domains, including help needed with eating, transfer (e.g. from bed to chair), grooming, bathing, toileting, walking, climbing stairs and dressing as well as presence of anal and urinary incontinence. It comprises 10 items, and the total score ranges from 0 to 100, with lower scores indicating higher dependence.

While the Barthel and the Katz index measure dependence in basic activities of daily living, the interview-based IADL scale [24] includes more complex activities of daily living. It comprises 8 items assessing the ability regarding telephone use, shopping, food preparation, housekeeping, laundry, mode of transportation, responsibility for own medications, and handling finances. The total score ranges from 0 to 8, with lower scores indicating higher dependence.

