### Statistical analysis

Patients’ characteristics regarding all variables assessed will be reported as mean ± standard deviation for continuous normally distributed variables, as median (Q1; Q3) for continuous variables which are not normally distributed, and as numbers (%, valid % when values are missing) for categorical variables.

For the video-based evaluation of self-administration of medication, at first 15 raters will rate a small subset of the patient sample to check whether the proposed standardized evaluation form is feasible, objective, and reliable. The agreement between the 15 raters on the ratings for each patient will be evaluated using Kendall’s W for categorical data (single items) and intraclass correlation coefficient for continuous data (sum scores). If the agreement is sufficiently high (≥ 0.8), the total patient sample will be rated by 2 independent raters and agreement will be evaluated with Cohen’s kappa for categorical data and intraclass correlation coefficient for continuous data. To assess test–retest reliability of the video-based evaluation, 30 patients will perform the assessment again after 5 days, and the 2 raters, who rated the total patient sample, will rate patient performance again. Retest reliability will be calculated using Spearman’s Rho for continuous variables and Chi-square for categorical variables.

To evaluate which factors influence the ability to self-administer medication, correlation and regression analyses will be performed. For continuous scores describing the ability to self-administer medication, Spearman’s Rho will be used for analyzing continuous and ordinal factors and Chi-square for analyzing nominal factors. Curve estimation procedure will be used to check whether a linear regression model fits the data in case of bivariate continuous associations and variables will be transformed if necessary. Uni- and multivariable linear regressions models including interaction terms will be calculated to identify which factors influence the ability to self-administer medication to which degree. If linear associations are not met even with data transformation, non-linear regressions will be performed. Missing data will be excluded from analysis listwise. All statistical analyses will be performed using SPSS 22 for Windows (IBM Corporation, Armonk, NY, USA). All statistical tests will be 2-tailed and *p*-values < 0.05 will be considered significant.

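### The three falls-history levels overlap, leave one pattern of recurrent falling without a level, and code another as single falling

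*Protocol article*

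**What the plan says.** Under Motor function/functional state, the protocol article introduces the variable with "History of falls is assessed in a face-to-face interview and categorized as" and then lists three levels: "1 fall within the previous 12 months, 1 fall within the previous 3 months, or more than 1 fall within the previous 3 months". It gives no rule for a patient who meets two of them, and it does not say whether the result is an ordinal or a nominal variable.

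The Statistical analysis section tests candidate factors by scale level: Spearman's "Rho will be used for analyzing continuous and ordinal factors and Chi-square for analyzing nominal factors". It does not say which of these applies to falls history. On incomplete data it states "Missing data will be excluded from analysis listwise".

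Finding factors associated with the ability to self-administer medication is one of the main objectives, and falls history is among the motor-function measures collected for it. The sample is 100 patients, "admitted to the department of orthopedics and trauma surgery electively or via the emergency department".

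**The concern.** The list mixes two nested time windows with two counts. The shorter window separates one fall from more than one, but the longer window does not. An interviewer can therefore face a patient who fits two levels, or one who has fallen repeatedly and fits none. A third type, with one recent fall and one or more earlier ones, is placed, but with the code of a person who fell once.

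The distinction between single and recurrent falling over the year is thus largely lost at data collection and cannot be recovered at analysis. If patients without a level are treated as missing, the listwise rule removes them from any multivariable model that contains the variable, and all who are lost through this gap are repeat fallers.

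**Working it through.** **Step 1: enumerate the patterns.** Let *a* be the falls in the last 3 months and *b* the falls in months 4 to 12. The third level says more than one, so one fall is read as exactly one.

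| a | b | Levels met |
|---|---|---|
| 0 | 1 | first |
| 1 | 0 | first and second |
| 0 | 2 or more | none |
| 1 | 1 or more | second only, same code as a single recent fall |
| 2 or more | any | third |

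This needs no assumption beyond the wording. The second row is the overlap, the third row is the gap, and the fourth row is recurrence coded as single falling.

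**Step 2: try the looser reading.** Suppose the 12-month level means at least one fall. The gap closes. But every patient with a recent fall then also meets the first level, and patients with *a* = 0 and *b* of 2 or more are coded like patients with one older fall. Recurrence is still visible only in the third level.

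**Step 3: size.** There is no figure in the documents to reproduce, because no fall rate is given. The following are assumptions: a constant rate, so that a quarter of falls are expected in the last 3 months; a mean of *m* = 0.5 to 1.5 falls per year; and negative binomial counts with dispersion 1 (Poisson with a gamma-distributed rate of shape 1). With q = m/(1+m):

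- Recurrent (a+b ≥ 2): R = q²
- Recurrent, no level (a = 0, b ≥ 2): N = (1−q)(0.75q)²/(1−0.75q)
- Recurrent, second level (a = 1, b ≥ 1): S = 0.25q(1−q)[1/(1−0.75q)² − 1]
- Two levels met (a = 1, b = 0): D = 0.25q(1−q)

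At m = 1, q = 0.5:

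- R = 0.25
- N = 0.5 × 0.375²/0.625 = 0.1125
- S = 0.0625 × (1/0.625² − 1) = 0.0625 × 1.56 = 0.0975
- D = 0.0625
- N/R = 45%, S/R = 39%, together 84%

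| m | R | N | S | D | N/R | (N+S)/R |
|---|---|---|---|---|---|---|
| 0.5 | 11.1% | 5.6% | 4.3% | 5.6% | 50% | 89% |
| 0.8 | 19.8% | 9.3% | 7.7% | 6.2% | 47% | 86% |
| 1.0 | 25.0% | 11.3% | 9.8% | 6.3% | 45% | 84% |
| 1.5 | 36.0% | 14.7% | 13.8% | 6.0% | 41% | 79% |

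In 100 patients, column N means about 6 to 15 recurrent fallers without a level. Under the looser reading in step 2 these patients move to the first level, so the last column does not change.

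**Step 4: vary the model.** Across Poisson counts and negative binomial counts with gamma shape 1 or 0.5, at 0.3 to 3 falls per year, the share of recurrent fallers with no level is 29 to 55%. The share in the second level is 32 to 40%, and in the third 7 to 39%. The share not identifiable as recurrent is 61 to 93%.

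**Step 5: allow for the setting.** Suppose every patient had an index fall in the last 3 months on top of the rates in step 3. Nobody then lacks a level. The share of recurrent fallers in the second level is 0.75(1−q)/(1−0.75q), which is 67%, 63%, 60% and 55% at the four means. If one instead conditions on at least one fall in the last 3 months, with Poisson counts at 0.3 to 2 falls per year, the share is 72 to 84%.

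**The case against.** The strongest reply is that the scheme works with a little goodwill. If the highest applicable level is assigned, the overlap becomes simple nesting and the levels run from an older fall, through a recent fall, to repeated recent falls. If the 12-month level is taken as any fall not covered by a more recent level, the gap disappears, and with it any listwise loss. The article condenses a fuller document, where interview coding rules would normally stand. Many trauma patients may have had a recent fall, which shrinks the group without a level. Grip and pinch strength, the pegboard, DEMMI, Katz, Barthel and IADL cover motor and functional state more directly.

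Much of this stands. It rules out four stronger readings that a reader might infer:

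- *That the levels leave out most recurrent fallers.* Under the step 3 assumptions the share with no level is 41 to 50%. It passes half only under some low-rate assumptions, and the 79 to 89% is reached only by adding patients who do have a code.
- *That repeated falling cannot be recognised at all.* The third level is repeated falling, within 3 months and therefore also within 12.
- *That the variable has no valid order for Spearman's rho.* A highest-level rule would give one. The article never calls falls history ordinal, and it offers chi-square for nominal factors.
- *That the absence of a no-fall level is itself an error.* It may be implied when nothing applies, or lost in condensing, so no weight is put on it.

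The reply does not remove the core. The article states the levels, and the levels as stated conflict. No assignment rule, however sensible, separates one recent fall from one recent fall plus earlier ones, because the information is not in the code.

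**Conclusion.** The point holds in limited form. As written, the levels are not mutually exclusive and, with one fall read as exactly one, not exhaustive. Recurrent falling over 12 months is recognisable only when at least two falls were in the last 3 months. These statements follow from the wording alone.

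The size depends on assumed rates and on a constant rate over the year. In this setting the share without a level could be as low as zero if all patients had a recent index fall, but more than half of recurrent fallers would then still be hidden in the second level in the cases calculated. The loss through listwise exclusion arises only if patients without a level are treated as missing.

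Impact is modest. Falls history is one candidate factor among many; it is not an outcome, and no sample size or error rate depends on it. The change is worth making because it is cheap, serves a main objective and can still take effect: the article reports that recruitment is ongoing.

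**What to change.** Replace the three levels with two items: the number of falls in the previous 12 months (0, 1, 2 or more) and the number in the previous 3 months (0, 1, 2 or more). Analyse each as an ordered factor. Within each window the levels are exclusive and exhaustive, and the present three levels can be rebuilt from the two items, so nothing now collected is lost. For patients already enrolled, recode from the interview notes where these allow it, and report how many could not be fully recoded.

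The cost is one line on the case report form and a recode. The downside is that some early patients may stay only partly coded.
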